#### Analyses

Baseline characteristics and questionnaires will be presented and calculated for the intervention -, control and the whole group. Data will be collected in the database in electronic database REDCap. All feasibility measurements will be reported as numbers and percentages.

To assess the effect of exercise on the immune system in patients with NSCLC, key focus is on the composition of mobilized immune cells in peripheral blood, phenotypic changes of immune cells, changes in serum markers and infiltration of immune cells in tumor. Main studies on blood samples include flow cytometry analyses to study which cell types are mobilized, therefore, whole blood from all blood samples will be analyzed using a standard kit from BD Bioscience: 6-color TBNK Reagent with BD Truecount Tubes (Catalog No. 337166). Furthermore, flow cytometry (and potentially CYTOF) is used to measure frequencies and phenotypic changes of circulating NK cells, T cells, B cells, and MDSC within peripheral blood in response to exercise. Elisa and Luminex is used to study serum levels of a panel of markers (e.g., CRP, IL-6, adrenalin and noradrenalin).

For the infiltration of immune cells in tumor, immunohistochemistry will be used to analyze biopsy material for parameters such as NK cells, T cells, B cells, MDSC, tumor-associated macrophages (TAMs) and dendritic cells (DC) and PD-L1 expression on tumor cells. Finally, single cell sequencing of immune cell subsets, in particular NK cells and T cells, will allow detection of exercise mobilized cell that have migrated to the tumor. Overall, the format of RCT allows all analysis to be compared to a reference samples from the control group. Finally, data will be correlated with clinical characteristics (VO_2_ max, ORR, PFS, OS and questionnaires).

### Statistical analysis

Primary outcome is exercise-induced mobilization of NK cells among cancer patients. To be able to detect an average difference in NK cell count between patients in the intervention group and patients in the control group of 50%, with an estimated standard deviation of 40, and to obtain a type I error rate of 5% and a power of 80%, a sample size of 17 patients per study arm will be needed. To account for an expected dropout rate of approximately 50%, we decided to increase this number to a group size of 35. Hence, a total of 70 patients will be included in the study.

All randomized patients will be assessable for safety assessment. Response rates are defined as the sum of the percentage of patients who achieved complete and partial response in each group divided by the number of patients. PFS is defined as the time interval between the date of randomization and the date of disease progression or the date of death of any cause. Patients will be censored at the time of last clinical contact if they are lost to follow-up or do not experience disease progression or die before the cut-off date for the analyses. OS will be calculated from the date of randomization to the date of death of NSCLC and any cause or last contact (censored observation).

Overall response rates (ORR) will be compared between the treatment groups using the χ2 test. Other categoric data will be compared using Fisher΄s exact test. The Kaplan –Meier method is used to estimate the distribution of time to events (i.e., PFS and OS).

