### Intervention

Patients in the intervention group will receive an exercise-based intervention, in combination with standard treatment being immunotherapy, immunotherapy combined with chemotherapy or oncological surveillance. The exercise intervention consists of supervised and team-based (maximal team size: 5 participants) aerobic exercise training, three times a week for six weeks. Each training session will take approximately one hour, with effective time of training being ~ 40 min. Each training session will be initiated with 5 min of warm-up on a bicycle ergometer (Motion cycle 200 med, Emotion Fitnes GmbH & CO, Hochspeyer, Germany), followed by 5 × 2 min warm-up circuit training on: 1) an air bike ergometer (ReNegaDE AIR BIKE C2, Taiwan), 2) a ski ergometer (CONCEPT 2 Deutschland GmbH, Hamburg, Germany), 3) a rowing ergometer (Hiit Console, Core Health & Fitness LLC, Vancouver, USA), 4) a cross trainer (motion cross 600, Emotion Fitnes GmbH & CO, Hochspeyer, Germany), and, 5) exercises on a step bench. There will be 30 s between each exercise station for shifting. If a patient is unable to perform one of the exercises in the warm-up circuit training, it will be replaced by the bicycle ergometer. After the circuit training, the participants will shift to the bicycle ergometers for the rest of the session. The bicycle training will be initiated with 2 min start-up bicycling, followed by 3 × 3-min sequences of high intensity interval training constantly shifting between: A) 20 s at 85–95% MWL (as hard as you can go for 20 s) and B) 20 s rest interval (pedal easy). The high intensity interval sequences will be separated by two steady state sequences, each lasting 3 min. The training session will be finished off with 2 min of cool down cycling (pedal easy) and 2 min of stretching. Finally, a short session of mental relaxation will round up the training session for the participants. An overview of a training session is illustrated in Fig. 1.

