#### Clinical data

Clinical data, in the form of time of diagnosis, tumor stage, treatment regimen, ECOG PS, and comorbidities as assessed by Charlson comorbidity index (CCI) [39], weight, height, body mass index (BMI), hematology/biochemistry, and medication will be registered and assessed from medical records. CT scan of the thorax and abdomen is required at baseline (within 28 days before inclusion). Tumor response will be evaluated at baseline and at following CT scans (every 3 months according to the standard) and according to the RECIST 1.1 and iRECIST. To investigate whether the intervention may affect PFS and OS, recurrence and death (cancer-related and other causes) will be registered throughout the intervention period and during follow-up from medical records.

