#### Feasibility and safety

Feasibility of the intervention will be evaluated as attrition and adherence. Attrition is the number of patients who do not complete the study (dropouts). Adherence to the intervention will be assessed as the number and percentage of attended training sessions. An adherence rate of 70% is set as criteria for fulfilling the exercise program. Safety (adverse events) and tolerability will be evaluated at every training session and documented within the electronic case report form in REDCap. Finally, safety and adverse events will be documented according to Ethics Committee at Capital Region requirements.

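### PFS is censored at last clinical contact although tumour status is read on three-monthly CT, so time after the last scan counts as progression-free in both arms

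*Protocol article*

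**What the plan says.** The Protocol article, Statistical analysis, measures PFS from randomization to progression or death, whatever the cause of death. It then fixes the censoring date: "Patients will be censored at the time of last clinical contact if they are lost to follow-up or do not experience disease progression". The sentence goes on to cover patients who have neither progressed nor died by the analysis cut-off, so the rule reaches every censored patient. OS is also censored at last contact, in the sentence that follows.

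The Clinical data section sets out how disease status is observed: "Tumor response will be evaluated at baseline and at following CT scans (every 3 months according to the standard"), using RECIST 1.1 and iRECIST. Recurrence and death "will be registered throughout the intervention period and during follow-up from medical records". The stated purpose is "To investigate whether the intervention may affect PFS and OS", and Study endpoints lists PFS among the secondary endpoints.

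The Intervention section gives the exercise arm "aerobic exercise training, three times a week for six weeks". What is checked at those visits is described under Feasibility and safety: "Safety (adverse events) and tolerability will be evaluated at every training session". Tumour assessment is not mentioned there.

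**The concern.** A clinical contact shows that a patient is alive, which makes it a sound censoring date for OS. It does not show that the tumour has not grown. With CT as the scheduled tumour assessment, freedom from progression is documented only up to the last evaluable scan. The stated rule carries each censored patient beyond that date as if still known to be progression-free.

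This is a rule the article states, not a detail left to another document. If scans stay on schedule, the undocumented time is at most about 3 months per censored patient. If a patient stops being scanned but is still seen, it can be longer. Such patients stay in the risk set at later scan dates, where they cannot contribute a scan-detected progression, and the Kaplan–Meier curve is pushed up. At stake is the level of the PFS curves, and so any PFS figure that is reported or correlated with the immune data.

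**Working it through.** **No plan figure to reproduce.** The article gives no PFS median, event count, hazard ratio or power. The check has two parts.

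**1. Which dates can differ.**
- Training sessions: 3 per week × 6 weeks = 18, all in weeks 1–6.
- First follow-up CT: about 3 months, taken as week 13.
- Scheduled blood samples (Blood samples section): both arms at baseline, week 7–8 and week 11–12; controls also at week 4. The exercise arm's extra samples are drawn around three training sessions in weeks 1, 3 and 6.

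The 18 sessions can therefore move a censoring date only for patients lost during training, by at most about 6 weeks, and before any scheduled follow-up scan.

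**2. Size, by simulation.** All rates here are assumptions, not figures from the article:
- no treatment effect, and 100,000 patients per arm per scenario;
- median time to progression 26 weeks, detected at the next 13-weekly CT;
- median time to death without progression 200 weeks;
- cut-off uniform over weeks 26–104;
- early dropout 20% or 50%, in weeks 0–6;
- a share of the remaining patients stops scanning at a time uniform over weeks 13–52 but stays in contact for a set period.

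PFS is estimated by Kaplan–Meier, S(t) = ∏(1 − dᵢ/nᵢ), once with each censoring rule. The ranges below span both arms and both dropout rates at week 52.

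| Scenario | Last contact | Last CT | Difference (points) |
|---|---|---|---|
| Scans run to last contact | 0.208–0.211 | 0.206–0.207 | 0.2–0.5 |
| 20% stop scanning, contact 13 weeks more | 0.226–0.231 | 0.202–0.205 | 2.4–2.6 |
| 20% stop, 26 weeks more | 0.242–0.244 | 0.200–0.202 | 4.2–4.3 |
| 40% stop, 26 weeks more | 0.282–0.286 | 0.194–0.199 | 8.6–8.9 |

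The estimated median was 26.0 weeks under both rules in every scenario.

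**Benchmark.** The assumed model implies a 52-week PFS of 2^(−52/26) × 2^(−52/200) = 0.250 × 0.835 = 0.209.
- With scans up to last contact, the stated rule (0.208–0.211) is close to this.
- Where scanning stops early, it is too high by 0.226 − 0.209 = 1.7 points up to 0.286 − 0.209 = 7.7 points.
- The last-CT rule is slightly low, by 0.209 − 0.207 = 0.2 points up to 0.209 − 0.194 = 1.5 points, because deaths after the last scan still count while survivors have already left the risk set.

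**Difference between arms.** With 50% early dropout and no stopped scanning, the gap between the two rules at week 13 is 0.678 − 0.671 = 0.7 points in the exercise arm and 0.675 − 0.672 = 0.3 points in the control arm. The arm difference is 0.4 points. Nowhere at weeks 13, 26, 39 or 52 was it larger than about 0.4.

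**The case against.** The best defence is that the effect depends on behaviour the article does not predict. If scanning continues up to the last contact, the two rules differ by at most half a point, and the stated rule is then close to the model's own value. The larger gaps need 20–40% of patients to leave CT while still being seen, and nothing in the article says this is expected. Recurrence is also taken from medical records, so a contact may carry some information about progression. The bias is nearly the same in both arms, PFS is secondary, and the article names only Kaplan–Meier estimation for it. All of this stands, and it limits the severity. It does not make a contact equivalent to a tumour assessment.

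Two stronger readings are tempting. A reader might infer that the rule favours exercise because that arm is seen 18 more times. The documents do not support this. Those sessions end before the first follow-up CT, the scheduled contacts after training are the same in both arms, and no difference in contact or scanning after week 12 is stated. A patient lost at week 6 is out of the risk set before scheduled scans can show progression, whichever rule applies.

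A reader might also apply the expected dropout of about 50% to the 70 patients and conclude that 35 are affected. That dropout rate enlarges the sample for the NK-cell outcome, and Feasibility and safety defines dropouts as patients not completing the study. Neither implies loss of CT follow-up, which runs to the clinical standard.

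**Conclusion.** The point holds as a minor one. The PFS censoring rule does not match the way tumour status is observed, and time after the last evaluable scan is counted as progression-free in both arms. Relative to last-scan censoring, the 52-week estimate is higher by about 0.2–0.5 points if scans run to last contact. It is higher by about 2.5–9 points if 20–40% of patients stop scanning while contacts go on for 13–26 weeks. In the first case the practical harm is negligible; in the second the curve is clearly too high. These sizes rest wholly on the assumed progression, death, cut-off and scanning rates.

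The comparison between arms is hardly touched, and the training visits should not be cited as a source of material bias. The primary NK-cell outcome is unaffected.

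**What to change.** Replace the PFS censoring sentence with a rule along these lines: patients without progression or death are censored at the date of their last evaluable tumour assessment, or at randomization if there is none after baseline; deaths without prior progression remain events. Keep last contact as the censoring date for OS only. It would help to add how a progression or death that follows missed scans is handled, since that is where the two rules part.

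The cost is one sentence and slightly shorter PFS follow-up. Under the assumptions above, keeping late deaths as events makes the new estimate 0.2–1.5 points low at 52 weeks. That is smaller than the 1.7–7.7 points by which the present rule is too high when scanning stops before contact does.

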**Methods:**

HI AIM (NCT04263467) is a randomized controlled trial (70 patients, 1:1) for patients with non-small cell lung cancer. Patients in the treatment arm, receive an exercise-intervention consisting of supervised and group-based exercise training, comprising primarily intermediate to high intensity interval training three times per week over 6 weeks. All patients will also receive standard oncological treatments; checkpoint inhibitors, checkpoint inhibitors combined with chemotherapy or oncological surveillance. Blood samples and biopsies (ultrasound guided), harvested before, during and after the 6-week training program, will form basis for immunological measurements of an array of immune cells and markers. Primary outcome is circulating NK cells. Secondary outcome is other circulating immune cells, infiltration of immune cells in tumor, inflammatory markers, aerobic capacity measured by VO_2_ max test, physical activity levels and quality of life measured by questionnaires, and clinical outcomes.

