### Patients

A total of 70 patients with metastatic NSCLC will be recruited from Department of Oncology, at Herlev and Gentofte Hospital. Screening for eligible patients will be carried out by the oncologists in the department. Patients are required to sign an informed consent prior to inclusion and the research team will obtain ICF and all relevant baseline data before randomization. These will be stored according to danish legacy.

Patients are eligible for inclusion if the following inclusion criteria are fulfilled: 1) Diagnosed with metastatic NSCLC, 2) Measurable disease according to RECIST 1.1, 3) Age ≥ 18 years, 4) Treatment with CPIs, CPIs combined with chemotherapy or oncological surveillance, 5) Eastern Cooperative Oncology Group (ECOG) performance status score (PS) ≤ 2, 6) Preferable metastasis suitable for biopsy, 7) Normal bone marrow function, and, 8) Willingness to give informed consent for participation in the study.

Exclusion criteria are: 1) Any physical condition that hinder the execution of physical exercise, 2) Severe dyspnea that hinder the execution of high intensity aerobic exercise training, 3) Symptomatic brain metastases, 4) Dementia, psychotic disorders, or other cognitive diseases or conditions that hinder participation in a clinical exercise-based trial, 5) Unstable medical disease or history of serious or concurrent illness; any medical condition that might be aggravated by exercise training or that cannot be controlled, including, but not restricted to congestive heart failure (NYHA class III-IV), unstable angina pectoris, implantable cardioverter defibrillator (ICD), or myocardial infarction within 6 months, 6) A condition requiring systemic treatment with either corticosteroids (> 10 mg daily prednisone equivalents) or other immunosuppressive medications. Inhaled or topical steroids and adrenal replacement doses ≤ 10 mg daily prednisone equivalents are permitted. 7) Use of beta blockers, 8) Any systemic infections within the last 4 weeks, 9) Bone metastases, where exercise training increases the risk of pathological fracture as assessed by the treating physician.

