### Randomization

After inclusion, participants are randomly allocated to the intervention group or control group, using a 1:1 block randomization. ‘Blockrand’ package of the statistical software R was used to generate all randomization lists, and block size will only by known by the statistician setting it up. Randomization will be administrated via the web-based research platform REDCap (Research Electronic Data Capture). Randomization will be stratified according to treatment being: Immunotherapy, immunotherapy combined with chemotherapy or oncological surveillance. Source codes to generate all randomization lists are stored to ensure full reproducibility.

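### The ORR definition divides by the number of patients twice, and the chi-square named for ORR leaves out the randomisation strata, which makes it valid but conservative

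*Protocol article*

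**What the plan says.** All places are in the protocol article.

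- **Definition (Statistical analysis).** The response rate is the "sum of the percentage of patients who achieved complete and partial response in each group divided by the number of patients".
- **Test (Statistical analysis).** "Overall response rates (ORR) will be compared between the treatment groups using the" chi-square test. No stratification or adjustment is mentioned. The next sentence begins "Other categoric data will be compared using Fisher", so the choice of chi-square for ORR is deliberate.
- **Design (Randomization).** "Randomization will be stratified according to treatment being: Immunotherapy, immunotherapy combined with chemotherapy or oncological surveillance". Allocation is 1:1.
- **Population (Patients).** Every patient must have "Measurable disease according to RECIST 1.1", and surveillance is one of the three eligible treatment situations. No section removes or separates the surveillance patients when ORR is analysed.
- **Status (Study endpoints).** ORR is a secondary endpoint. The article gives no assumed response rate, no power for ORR and no expected share of patients per stratum.

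**The concern.** There are two separate matters in the same few sentences.

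1. A percentage of patients in a group already has the group size as its denominator. Dividing by the number of patients again gives a quantity that is not a response rate and that depends on arm size. Two arms with the same true rate would show different values if their sizes differed.

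2. Randomisation was stratified by background treatment, a plausible determinant of tumour response. Stratified randomisation balances the arms on that factor, so differences between strata no longer add to the variance of the arm contrast. A plain chi-square still counts them in its error term. If response differs between strata, the standard error is too large, the test rejects too seldom under the null, and power is given away in a trial of 70 patients. A single overall rate per arm also hides what happens in each treatment situation.

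**Working it through.** The article states no ORR figure, so there is no number of the plan's own to reproduce. The planned arm size of 35 comes from Statistical analysis. All stratum shares and response rates below are assumptions.

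**Step 1: the definition read literally.** With r responders among n patients the response rate is 100·r/n. The literal formula gives (100·r/n)/n.

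- r = 10, n = 35: 100 × 10/35 = 28.6%. Literal: 28.57/35 = 0.82%.
- True rate 30% in both arms, arms of 33 and 37: 30/33 = 0.91 against 30/37 = 0.81. The gap comes from arm size alone.

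A chi-square test uses the counts of responders and non-responders, so the formula does not enter it.

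**Step 2: size of the unstratified test, by formula.** Let stratum k have share w_k, the same in both arms, and response rate p_k. Let p̄ = Σ w_k p_k. With n patients per arm:

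- variance that the pooled test uses: (2/n) · p̄(1 − p̄)
- variance of the arm difference under balanced strata: (2/n) · Σ w_k p_k(1 − p_k)
- R = square root of the first over the second
- actual two-sided size of a nominal 5% test ≈ 2[1 − Φ(1.96·R)]

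| Assumed shares | Assumed rates | p̄(1 − p̄) | Σ w p(1 − p) | R | Actual size |
|---|---|---|---|---|---|
| equal thirds | 0, 25, 50% | 0.1875 | 0.1458 | 1.134 | 2.6% |
| equal thirds | 2, 30, 30% | 0.1640 | 0.1465 | 1.058 | 3.8% |
| 10, 45, 45% | 0, 30, 45% | 0.2236 | 0.2059 | 1.042 | 4.1% |

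The first rate in each row belongs to surveillance. For the last row, p̄ = 0.45 × 0.30 + 0.45 × 0.45 = 0.3375, and the within-stratum variance is 0.45 × 0.21 + 0.45 × 0.2475 = 0.2059. If all p_k are equal, R = 1 and nothing is lost.

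**Step 3: simulation at 35 per arm** (40,000 runs per case). It compares the pooled chi-square without continuity correction with a stratified Cochran-Mantel-Haenszel (CMH) test, two-sided 5%. Rates are in the order checkpoint inhibitor (CPI), CPI plus chemotherapy, surveillance. Power is for +20 percentage points in the two CPI strata only.

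| Patients per stratum and arm | Rates (%) | Size, chi-square | Size, CMH | Power, chi-square | Power, CMH |
|---|---|---|---|---|---|
| 12, 12, 11 | 30, 50, 0 | 0.025 | 0.050 | 0.196 | 0.310 |
| 12, 12, 11 | 30, 50, 2 | 0.029 | 0.052 | 0.201 | 0.296 |
| 12, 12, 11 | 40, 50, 5 | 0.032 | 0.048 | 0.178 | 0.268 |
| 12, 12, 11 | 20, 60, 0 | 0.017 | 0.049 | 0.180 | 0.329 |
| 15, 15, 5 | 30, 50, 0 | 0.038 | 0.048 | 0.272 | 0.353 |
| 15, 15, 5 | 30, 50, 2 | 0.038 | 0.048 | 0.274 | 0.355 |
| 15, 15, 5 | 40, 50, 5 | 0.040 | 0.053 | 0.258 | 0.342 |
| 15, 15, 5 | 20, 60, 0 | 0.026 | 0.051 | 0.252 | 0.393 |

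The chi-square stays below 5% in every case (0.017 to 0.040) and CMH is close to nominal (0.048 to 0.053). Power is 0.18 to 0.27 against 0.27 to 0.39.

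**The case against.** **The definition is only a slip.** The sentence names the right ingredients: complete and partial responders, per group, over patients. The intended quantity is clear, and a result of 0.8% is unlikely ever to be reported. This stands, and it makes the repair editorial. The sentence is still the published definition of a named secondary endpoint and is wrong as written.

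**The unstratified test is not an error.** After stratified randomisation a plain chi-square keeps its false-positive rate at or below nominal. Power for ORR is low with either test, and the Discussion itself says that efficacy needs bigger trials. This stands: the choice of test would hardly change what this trial can conclude about response.

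**Stratified adjustment is commonly left to the SAP, which is not shown.** That would dispose of the matter if the article were silent on the test. It names one, and the named test does not use the design. An unseen SAP may already add the strata.

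**The size depends on chosen inputs.** This stands too. Equal thirds with 0, 25 and 50% favours the concern. With a 10% surveillance share and 30% and 45% elsewhere, the actual size is about 4.1%, a trivial departure.

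**A stronger reading about surveillance.** A reader might infer that surveillance patients receive no tumour treatment, cannot respond, and so only dilute the ORR. The documents do not say this. Surveillance is never defined, the abstract says "All patients will also receive standard oncological treatments; checkpoint inhibitors, checkpoint inhibitors combined with chemotherapy or oncological surveillance", and measurable disease is required of everyone, so response can be assessed in all three strata. A reader might also carry the point over to PFS and OS, but for those the article names only Kaplan-Meier estimation and no comparison test.

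**Conclusion.** The point holds in a limited form.

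- The ORR definition is misstated by a second division by the number of patients. With arms of 35 the literal result is too small by a factor of 35. Only a rate reported from that formula is affected, not the test.
- The named chi-square is valid but conservative whenever response differs between the treatment strata. Under the assumed shares and rates its actual size is roughly 2 to 4% instead of 5%, and it gives up about 8 to 15 percentage points of power against a stratified test in the simulated cases (smallest gap 0.353 − 0.272 = 0.081; largest 0.329 − 0.180 = 0.149).

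The direction follows from the design and needs only that response differs between strata and that the strata are about balanced between arms. The magnitude rests on assumed shares and rates. The consequence is modest: a secondary endpoint, low power in any case, and no risk of a false-positive claim. The change is worth making because it costs no patients and no data.

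**What to change.** 1. Define ORR as the number of patients with complete or partial response divided by the number of randomised patients in the arm. Correcting the formula does not by itself require the randomised denominator, but the article says only that the divisor is the number of patients while expecting about 50% dropout, so the denominator should be stated.
2. Replace the plain chi-square for ORR with a Cochran-Mantel-Haenszel test stratified by the three randomisation strata, using an exact version if the tables are sparse.
3. Show ORR per stratum and arm beside the overall figure, so that the surveillance stratum is visible and readers can judge its contribution.

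Cost: a few lines in the SAP or in a protocol clarification. The stratum is already a factor in the REDCap randomisation, so no new data are needed. The article reports 23 of 70 patients included as of January 2022, so at that stage the change could still be made well before the final analysis.
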